### Sample size - power analysis

The calculations rely on the high effect size of our primary outcome (d = 1.09 for the composite pain score; see [21, 22]) and correlation among repeated measures 0.8 (see [20–22]). Since our recent single-site study included a 3-month follow-up and a waiting list control group (instead of an active control group [21, 22]), power analysis for the primary outcome is based conservatively on a medium effect size (f = 0.25; d = 0.6). Independent variables are intervention (2), gender (2), age (2) and site of intervention (5), forming a total of 2^3^*5 = 40 groups.

In the study centers, n = 450 children will be assessed for eligibility and a total number of n = 112 children will be allocated to the trial (n = 56 in IG, n = 56 in CG). We assume a drop-out rate of 20% [cf. 18], resulting n = 112 children to be analyzed in the intention-to-treat analysis (ITT) and n = 90 children for the per protocol analysis (PPA).

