### Randomization

Allocation sequences are generated centrally at the Institute of Epidemiology at University Clinic of Hamburg-Eppendorf (KW). It will be mutually randomized in IG and CG with a 1:1 ratio. Each patient’s position on allocation sequence is defined by computer-generated random-numbers and the date of informed consent (chronologically sorted).

As groups are assigned parallel and the interventions are to be carried out mutually, blocking is dependent on the group sizes. Block sizes range between 6 and 16 patients. The total number of each block is dependent on the total number of groups to be trained. As in this trial, a maximum of 25 groups are to be trained; the number of blocks of 6 and 8 patients is restricted to five each.

The randomization procedure, in order to prevent selection bias, occurs centrally at the University of Potsdam by a person not involved in the intervention process and data analysis. We realize a stratified (according to center) block randomization. Randomization and allocation to interventions occur after assessment of pre-data and before the interventions start. Results of randomization will be provided directly only to the trainers via email (allocation concealment). Each center has to realize four different groups; at the first block of interventions, the trainer may choose the trial arm (IG versus CG); in the second block, the trainers have to change the trial arm.

The effectiveness of the randomization is evaluated post-hoc by descriptive statistical comparisons between IG and CG in known and presumed baseline predictors of treatment success (for example, pain history of the parents and socio-economic status) and relevant sociodemographic data (age and sex).

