### Primary analysis of the primary endpoints

An analysis of covariance will be performed in the ITT population, comparing the log area under the pain intensity curve from intervention to 12-month follow-up between the two random groups adjusted for the baseline measurements. Length of pain episodes will be analyzed analogously. Frequencies will be analyzed using a Poisson regression model.

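### Centre stratifies the randomisation and is a factor in the power analysis, but the confirmatory ANCOVA names only baseline; if centres differ, the test is modestly less efficient than it could be

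*Protocol article*

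**What the plan says.** Three sections of the protocol article bear on this.

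- **Randomization:** "We realize a stratified (according to center) block randomization". The ratio is equal: "It will be mutually randomized in IG and CG with a 1:1 ratio". Under Intervention and controls, all five centres run both arms.
- **Sample size - power analysis:** "Independent variables are intervention (2), gender (2), age (2) and site of intervention (5), forming a total of" 40 groups. The planned sample is 112 ("n = 56 in IG, n = 56 in CG"), and the assumed effect is given as both f = 0.25 and d = 0.6.
- **Primary analysis of the primary endpoints:** the log area under the pain intensity curve is compared by ANCOVA in the ITT population "between the two random groups adjusted for the baseline measurements". Episode length is to be handled in the same way, and frequency by Poisson regression. Centre is named in none of these.

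Confirmatory analysis makes the log AUC comparison the gate to the tests of number and length of episodes. The mixed model under Analysis of secondary outcomes carries a random therapist effect and several baseline variables.

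**The concern.** Blocked 1:1 allocation within centre largely removes centre differences from the treatment contrast. A model without centre does not recognise this and counts the same differences as residual noise. If such differences remain after baseline adjustment, the reported standard error is larger than the true one and the test gives away some of the precision that stratification provides. The confirmatory model also fails to match the design and the factor list in the sample-size section. Because the log AUC test opens the hierarchy, any efficiency lost there carries through to the tests of number and length of episodes.

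**Working it through.** **Inputs from the article.** 56 children per arm, 5 centres, blocked 1:1 allocation within centre, d = 0.6, f = 0.25 and "correlation among repeated measures 0.8". For two equal groups d = 2f, so f = 0.25 corresponds to d = 0.5. Both values of d are therefore carried.

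**Assumptions.** The article states neither power nor sidedness; 80% and two-sided 5% are assumed. It gives no centre variance. Let *s* be the between-centre share of the variance left after baseline adjustment, taken over 0 to 0.20, with that total variance set to 1.

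**Step 1: reproduce N = 112.** Take a repeated-measures test of the between-subject treatment effect (1 df) with noncentrality λ = f²·N·m/[1 + (m − 1)ρ]. With f = 0.25, ρ = 0.8, m = 3 measurements and 40 cells, N = 112; with m = 4, N = 110. A two-sample t-test at d = 0.6 needs 45 per arm, and 90/0.8 = 112.5. So 112 reproduces. With 2 cells instead of 40 (m = 3), N is 111. Site therefore hardly affects the planned number: the calculation spends degrees of freedom on it and takes no credit for reduced variance.

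**Step 2: effect of leaving centre out (analytic).**

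- Model SE without centre: √(2/56) = 0.189.
- True SE under balance within centre: 0.189·√(1 − s).
- True type I error without centre: 2Φ(−1.96/√(1 − s)).
- Power without centre: Φ[(d − 1.96·0.189)/(0.189·√(1 − s))].
- Power with centre: Φ[d/(0.189·√(1 − s)) − 1.96].

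Example, s = 0.10 and d = 0.6: the true SE is 0.179. Without centre, (0.6 − 0.370)/0.179 = 1.28, power 0.900. With centre, 0.6/0.179 − 1.96 = 1.39, power 0.917.

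| s | SE overstated by | type I, no centre | power d = 0.5, without / with | power d = 0.6, without / with |
|---|---|---|---|---|
| 0 | 0% | 5.0% | 75.4 / 75.4% | 88.8 / 88.8% |
| 0.05 | 2.6% | 4.4% | 75.9 / 77.5% | 89.4 / 90.3% |
| 0.10 | 5.4% | 3.9% | 76.5 / 79.6% | 90.0 / 91.7% |
| 0.20 | 11.8% | 2.8% | 77.8 / 84.1% | 91.3 / 94.4% |

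**Step 3: simulation.** 112 children in centres of 22, 22, 22, 22 and 24, arms balanced within centre, least squares with and without centre indicators, 20,000 data sets per setting. For s = 0.05, 0.10 and 0.20:

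- True type I error without centre is about 4.8%, 4.2% and 3.6%.
- Power at d = 0.5, without v with centre, is 75.1% v 76.3%, 76.4% v 79.0% and 78.2% v 83.3%. The differences are 1.2, 2.6 and 5.1 points.
- At d = 0.6 the differences are about 0.8, 1.7 and 2.5 points.
- At s = 0 power at d = 0.5 is 73.6% either way.

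Repeat runs of 40,000 to 60,000 data sets stay close: type I error of 4.5% to 4.7%, 4.0% to 4.1% and 3.3% to 3.5%. The simulated effects are somewhat milder than the analytic ones because five centre effects are drawn at random, and their spread averages 4/5 of the nominal variance.

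**Step 4: the opposing effect of training groups.** Both arms are delivered in groups of 3 to 8 children, and the ANCOVA ignores this. With design effect 1 + (m − 1)·ICC, where m is now the group size, and an assumed ICC of 0.02 to 0.10, the SE is understated by a factor between √1.04 = 1.02 (m = 3, ICC 0.02) and √1.70 = 1.30 (m = 8, ICC 0.10). In simulation with two groups per arm per centre and an assumed group share of 5% to 10%, true type I error is about 6% to 11% without centre and 8% to 12% with it.

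**The case against.** - **The effect is conditional.** It needs centre differences that survive baseline adjustment. With a correlation of 0.8 among repeated measures, the baseline covariate may already remove much of any stable centre difference in pain level. This stands: the loss may be close to zero.
- **Planned power.** A reader might infer that the omission leaves the trial short of its planned power. The documents do not support that. N = 112 takes no variance credit for site, and at d = 0.6 with a 10% share the model without centre has power 0.900 against 0.888 at zero share. What is lost is a gain that the better model would bring.
- **Direction.** A reader might infer that the confirmatory test in this trial is conservative. That follows only with centre considered alone. Group delivery pushes the standard error the other way by an amount the documents do not fix, and adding centre while ignoring groups makes that second error slightly more visible. This limits what can be claimed, but two errors of unknown size and opposite sign do not justify leaving out the stratification factor.
- **The mixed model.** A reader might extend the point to the secondary mixed model, which also names no centre. There are 10 trainers for 5 sites. If each trainer works at one site, which is likely but not stated, the random therapist effect may already absorb much of the centre variance. The point is not made for that model.
- **Condensed article.** A full covariate list is often left to the analysis plan, and the ANCOVA sentence does not expressly exclude other covariates. But it does state what the confirmatory comparison adjusts for, and that statement does not match the randomisation and sample-size sections. The mismatch can be reviewed as it stands.

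**Conclusion.** The mismatch is real: the trial randomises within centre and counts site as a factor, but the stated confirmatory model adjusts for baseline alone. The consequence is a modest loss of efficiency, conditional on centre differences remaining after baseline adjustment. For assumed residual shares of 5% to 20%, it is about 1 to 5 points of power at d = 0.5 and 0.8 to 2.5 points at d = 0.6, with true type I error of about 4.8% down to 3.6% when centre is considered alone. These figures rest on an assumed centre share, two-sided 5%, balance within centres and 112 analysed children. The omission by itself neither inflates type I error nor takes power below plan. The net direction of the standard error cannot be settled without the clustering by training group. The point is worth correcting because the correction is nearly free and concerns the test that gates the hierarchy.

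**What to change.** Before the regular unblinding that follows entry of the last T4 data, state that centre enters as a fixed factor beside the baseline value in the primary ANCOVA of log AUC, in the analogous analysis of episode length and in the Poisson model for frequency. If centre is to be left out, give the reason. The sample-size section and the analysis section would then describe the same design.

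The cost is wording and 4 degrees of freedom: residual degrees of freedom in the ANCOVA go from 112 − 3 = 109 to 105. No additional data are needed, and almost no power is lost if centres are alike. The centre term does not deal with clustering by training group. That needs its own decision and should be settled at the same time, so that the smaller residual is not taken as proof of a correct standard error.

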### Analysis of secondary outcomes

Further, we will analyze primary and secondary outcome measures using a mixed model, adjusting for the therapist (random effect) and baseline measures (including age, gender, duration of illness, age at onset and the baseline measure of the outcome of interest).

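### The confirmatory ANCOVA does not name centre, the only randomisation stratum, and leaves open whether age and gender are covariates, although the power model contains all three

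*Protocol article*

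**What the plan says.** Four sections of the protocol article bear on the model for the primary outcome.

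- **Primary analysis of the primary endpoints:** an ANCOVA in the ITT population compares log-AUC pain intensity "between the two random groups adjusted for the baseline measurements". Those measurements are not listed. Length of episodes is handled the same way, and frequency by Poisson regression.
- **Sample size - power analysis:** "Independent variables are intervention (2), gender (2), age (2) and site of intervention (5"), which makes 40 cells. The effect size "is based conservatively on a medium effect size (f = 0.25; d = 0.6"), with "correlation among repeated measures 0.8".
- **Analysis of secondary outcomes:** primary and secondary outcomes are also put into a mixed model with therapist as a random effect and "baseline measures (including age, gender, duration of illness, age at onset and the baseline measure of the outcome of interest") as covariates.
- **Randomization:** "It will be mutually randomized in IG and CG with a 1:1 ratio", in blocks, stratified by centre and by nothing else.

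**The concern.** The power model, the deciding test and the supportive model of the same outcome have three different covariate sets as written. The deciding test has the shortest.

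Centre is the clearest gap. Stratifying by centre balances the arms within centres, so differences between centres add little to the true variance of the treatment contrast. A model without centre still counts those differences as residual noise, so its standard error tends to be too large and the test conservative.

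Age and gender raise a smaller version of the same point. They were not stratified for, so omitting them does not make the standard error wrong. But whatever outcome variance they explain beyond baseline pain stays in the residual.

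There is also a risk of late choice. The Randomization section plans a post-hoc comparison of age and sex between arms, and the Descriptive analysis section plans tests of baseline differences. An open covariate list leaves room to settle the adjustment after seeing them.

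**Working it through.** **1. Which variables each section names**

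- Baseline pain: primary ANCOVA (as baseline measurements) and supportive model; not listed among the factors of the power model.
- Centre: randomisation and power model; not the primary ANCOVA. The supportive model has therapist, not centre.
- Age and gender: power model and supportive model; not named in the primary ANCOVA.

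**2. Reproducing the sample size**

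Inputs: "a total number of n = 112 children will be allocated to the trial (n = 56 in IG, n = 56 in CG"). The article expects 20% to drop out, leaving 90 per protocol. Alpha and power are not given with the calculation; 5% two-sided and 80% are assumed.

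- *Two-arm comparison, d = 0.6.* The exact noncentral t needs 45 per arm, so 90 in total, and 90/0.8 = 112.5. This fits the stated 90 and 112 and contains no centre, age or gender.
- *Repeated-measures group effect (1 df), f = 0.25, rho = 0.8, m = 3 measurements.* The noncentrality is f² × N × m / (1 + (m − 1) × rho) = 0.0625 × 112 × 3 / 2.6 = 8.08. For 80% power this needs N = 112 with 40 cells and N = 111 with 2 cells. With m = 4 the figures are 110 and 109.

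Either route gives about 112, and the extra factors change N by one child.

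**3. What age and gender could add**

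Let R² be the share of the variance left after baseline pain that age and gender explain. The documents do not give it, so a range is used. The effect becomes d/√(1 − R²). The noncentrality is that effect times √(56/2). Residual df fall from 112 − 2 − 1 = 109 to 107. Alpha is 5% two-sided.

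- Without age and gender: power 88.2% at d = 0.6; 74.6% at d = 0.5.
- R² = 0: 88.2%; 74.6%.
- R² = 2%: 88.8%; 75.4% (standard error 1.0% smaller).
- R² = 5%: 89.8%; 76.7% (2.5% smaller).
- R² = 10%: 91.3%; 78.9% (5.1% smaller).

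Both effect sizes are shown because the article's pair does not agree: for two equal groups f = d/2, so f = 0.25 is d = 0.5, and d = 0.6 is f = 0.30. That is a separate matter.

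The figures treat age and gender as balanced between arms. Chance imbalance raises the adjusted variance on average by about (112 − 4)/(112 − 4 − 2) = 108/106 = 1.019. That takes back roughly what an R² of 2% gives.

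**4. What centre adds**

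Five centres cost 4 df. If a share R² of the residual variance lies between centres, a model without centre reports a standard error too large by about 1/√(1 − R²). At an assumed 5% that is 1/√0.95 = 1.026, or 2.6%. The documents give no between-centre variance.

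**5. The price in degrees of freedom**

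Centre (4), age (1) and gender (1) take residual df from 109 to 103. With the formula of step 3 and R² = 0, power goes from 88.24% to 88.20% at d = 0.6 and from 74.61% to 74.57% at d = 0.5.

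**The case against.** The strongest reply is that nothing has been shown to be left out. The primary analysis speaks of baseline measurements in the plural. The section on secondary outcomes uses nearly the same term with age and gender inside it. A condensed article may also leave the exact list to the analysis plan. This stands in part: a reader might infer that age and gender are definitely excluded, and the text does not establish that. It does not dispose of the point. Centre is in neither list and is not a baseline measure in the article's usage. The article chose to spell out the factors of the power model and the covariates of the supportive model, and the two disagree with the deciding test on the page.

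A second reply is that age and gender do not drive the sample size and that omitting them does not bias a randomised comparison. Both statements are right. A reader might infer that the test is invalid or that planned power has been lost. Step 2 of the working does not support either.

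A third reply is that the gain rests on an R² nobody has stated. That is also right. A reader might argue that age must matter because the Blinding section has younger children followed up by telephone. But no age cut-off is given and nothing shows that the mode shifts scores. The primary outcome is a self-report diary, and the Points of measurement section has follow-up data collected by mail. No R² can be inferred from this.

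Finally, the supportive mixed model already gives an analysis adjusted for age and gender. It does, but it is not the confirmatory test and does not contain centre.

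**Conclusion.** The point holds as a matter of model specification and precision. As written, the confirmatory test omits the one factor on which randomisation was stratified and does not settle whether age and gender are in the model. It therefore does not match the model on which the trial was powered. Type I error is not inflated; ignoring the stratum tends towards conservatism.

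The size is modest. For age and gender the gain is 0 to about 3 power points at d = 0.6 and 0 to about 4 at d = 0.5, for an assumed R² of 0 to 10% beyond baseline pain, with 56 per arm and 5% two-sided alpha. It is nil, or slightly negative after chance imbalance, if R² is near zero, so the precision is nearly free but not guaranteed. The effect of centre cannot be sized from the documents, but its inclusion follows from the design and does not depend on an assumed gain. The change should be made; the trial does not fail without it.

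**What to change.** Before unblinding, state the primary model in the section on the primary analysis as log-AUC pain intensity on arm, baseline pain, centre, age (continuous) and gender. Use the same covariates for episode length and in the Poisson model for frequency. In the sample-size section, replace the 40-cell layout with this main-effects model, so that the stated power basis and the deciding test agree.

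The cost is a few sentences and about 6 of 109 residual degrees of freedom: 4 for centre, 2 for age and gender. No new data are needed. Centre is known from the randomisation, and age and sex are already to be compared between arms at baseline.

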### Outcome variables

#### Primary outcome measure

The primary outcome is the course of pain frequency and intensity of FAP (composite score) from pretreatment (T1) to post-treatment (T2), 3-month (T3) and 12-month follow-up (T4). Pain symptoms will be assessed via self-report using the pain diary, which has already successfully been implemented in prior trials [20–22]. On 14 consecutive days, children should report intensity of pain on a 10-point visual analog scale. Pain duration and frequency are derived from reports on time spans of when the pain arose.

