### Confirmatory analysis

In terms of clinical relevance, the composite pain score is the most prominent outcome: a substantial pain reduction is mandatory for treatment efficacy. We therefore apply a hierarchical testing procedure; the number and length of pain episodes will be tested only if there is a significant difference between the treatment groups in the log area under the curve (auc) of pain intensity. These endpoints will be tested to an alpha level of 2.5%; therefore, under this hierarchical design the overall alpha level of the trial will not exceed 5%.

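### The confirmatory test of pain-episode number is fixed as Poisson regression with no provision for overdispersion, so its 2.5% level is not assured

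*Protocol article*

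**What the plan says.** All references are to the protocol article.

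- **Model.** Under Primary analysis of the primary endpoints, intensity is compared by a baseline-adjusted analysis of covariance and episode length is handled in the same way. For frequency the article says: "Frequencies will be analyzed using a Poisson regression model". It names no scale parameter, robust variance or alternative count model.
- **Status.** Under Confirmatory analysis, "the number and length of pain episodes will be tested only if there is a significant difference between the treatment groups" in the intensity measure. Then: "These endpoints will be tested to an alpha level of 2.5" per cent, and "under this hierarchical design the overall alpha level of the trial will not exceed 5" per cent. Whether the tests are one- or two-sided is not said.
- **Data.** Under Primary outcome measure: "On 14 consecutive days, children should report intensity of pain on a 10-point visual analog scale". Also: "Pain duration and frequency are derived from reports on time spans of when the pain arose". The diary is kept at T1 to T4.
- **Elsewhere.** The mixed model under Analysis of secondary outcomes is a secondary analysis. The sensitivity analysis under Exploratory analyses concerns missing values only. Neither replaces or qualifies the confirmatory Poisson test.

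**The concern.** Poisson standard errors are right only if, given the covariates, the variance of the count equals its mean. If children differ in their underlying episode rate beyond what the covariates explain, the variance exceeds the mean. The standard errors are then too small and the test rejects too often.

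The article gives reasons to expect such differences. Eligibility sets a floor of one episode a week and no ceiling, four Rome III subtypes are enrolled, and the power section assumes a high within-child correlation ("correlation among repeated measures 0.8"), which implies stable differences between children.

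Frequency is half of the primary hypothesis. A false positive here would be reported as confirmatory evidence that the programme reduces how often pain occurs, with an error rate that the article says is controlled.

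**Working it through.** **1. The plan's own figure.** Two gated tests at 2.5% each give 0.025 + 0.025 = 0.05. This reproduces the stated 5%, provided that each test holds its own level.

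**2. True size under overdispersion.** Let φ be the variance/mean ratio left after covariates. A Poisson Wald statistic then has standard deviation √φ under the null. For a nominal two-sided 2.5% test:

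size = 2 × [1 − Φ(2.2414/√φ)]

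The documents give no φ, so the values below are assumed. The last column shows the one-sided 2.5% reading, 1 − Φ(1.96/√φ).

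| φ | 2.2414/√φ | two-sided size | one-sided size |
|---|---|---|---|
| 1.0 | 2.241 | 2.5% | 2.5% |
| 1.2 | 2.046 | 4.1% | 3.7% |
| 1.5 | 1.830 | 6.7% | 5.5% |
| 2.0 | 1.585 | 11.3% | 8.3% |
| 3.0 | 1.294 | 19.6% | 12.9% |

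The two-sided size reaches 5% at φ = (2.2414/1.9600)² = 1.31. Since φ = 1 + mean × CV², an assumed mean of 4 episodes per diary and a residual between-child coefficient of variation of 0.28 are enough: 1 + 4 × 0.0784 = 1.31.

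**3. Illustration with the article's correlation.** The 0.8 is not stated to apply to episode counts. If it did, and counts were Poisson given each child's own rate:

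- one diary, unadjusted: φ = 1/(1 − 0.8) = 5
- one diary, baseline-adjusted: φ = (1 − 0.64)/(1 − 0.8) = 1.8, size 9.5%
- three diaries summed, baseline-adjusted: φ = (3 + 4.8 − 5.76)/(3 × 0.2) = 3.4, size 22.4%

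**4. Simulation.** There were 56 v 56 children, no treatment effect, 1,500 runs per setting, and assumed means of 4 and 8 per diary. Monte Carlo standard error at 2.5% is √(0.025 × 0.975/1500) = 0.4 percentage points. All models are baseline-adjusted. For episodes, the single-diary φ before adjustment was 2 to 5. For pain days, the within-child correlation was 0.5 or 0.8.

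| What is counted | Poisson | Pearson scale | Robust |
|---|---|---|---|
| Episodes, one diary | 5.4–9.4% | 1.9–3.6% | 2.4–4.1% |
| Episodes, three diaries summed | 15.2–22.9% | 2.4–3.1% | 2.6–3.8% |
| Pain days capped at 14, one diary | 0.2–2.8% | 1.4–2.4% | 2.5–3.2% |
| Pain days, three diaries summed | 3.0–10.9% | 1.3–2.3% | 2.4–2.7% |

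Negative binomial regression was not simulated.

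**5. What this does to the 5% claim.**

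- *No effect on any endpoint.* A gated false positive first needs a false positive on intensity. The family-wise error cannot exceed the level of the intensity test, whatever the size of the Poisson test.
- *Intensity differs, frequency does not.* The gate opens with the power of the intensity test. If that power is assumed to be 80% and the tests are treated as independent, φ = 2 gives 0.80 × 11.3% = 9.0% from frequency alone, before length is counted.

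**The case against.** The article condenses a fuller document and gives one sentence naming a model family. A scale parameter, robust variance, an offset for completed diary days and the covariate list are commonly settled in the analysis plan, which is not shown. A reader might infer that the model has no offset, no within-child term and no variance correction. The article does not say so. It reduces intensity to one summary per child, and one count per child would fit equally well and need no within-child term. Those omissions are not part of this point. Clustering by training group is a separate matter.

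A reader might also infer that a several-fold inflation has been shown. It has not. No dispersion is reported, and the article does not say how severe pain frequency is above the entry floor. Baseline adjustment, stated only for the analysis of covariance, would absorb much of the between-child spread. If frequency means capped pain days in one diary, the adjusted Poisson test is at or below its level.

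These objections limit the size of the problem but do not remove it. The article positively names the model for a confirmatory endpoint and attaches an error-rate claim to it. Its confirmatory wording refers to the number of episodes, which has no cap at 14, and in that case inflation is likely.

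**Conclusion.** The point holds in conditional form. The confirmatory test of episode number is fixed as Poisson regression with no provision for overdispersion, so its 2.5% level is not assured.

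The true size is about 4% to 20% for an assumed residual variance/mean ratio of 1.2 to 3, reading the test as two-sided. There may be no inflation for capped pain days from one baseline-adjusted diary.

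It would be too strong to say that the overall 5% claim fails outright. The claim holds under the global null because of the gate, provided the intensity test is itself run at no more than 5%. It can fail when intensity truly differs and frequency does not, a case that a claim about overall alpha has to cover.

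The plan should be changed because the remedy is cheap and protects a stated error rate. The point does not affect the intensity analysis.

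**What to change.** Before unblinding, which the article places after the last T4 data are entered:

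1. Replace the Poisson model with negative binomial regression, or keep Poisson with a Pearson scale or a robust (sandwich) variance. In the simulation the robust variance stayed near its level for both episodes and capped days, though it ran slightly high in places (up to 4.1%). The Pearson scale stayed within 1.3% to 3.6%.
2. State what is counted, episodes or pain days, and use one count per child over the post-treatment diaries.
3. Adjust for baseline frequency in a form that is defined when the baseline count is zero. A plain logarithm is not.
4. If T2 to T4 enter as separate rows instead, use a robust variance at child level.

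The cost is a few lines of wording and no change to design or data collection. If the counts are truly Poisson, some power is lost. The loss should be small, but it was not calculated here.
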